### Objectives and hypotheses

Therefore, the aim of this study is to use SPs to evaluate specific training and supervision conditions. Psychology students will be taught distinct interventions relevant for the cognitive behavioral therapy of patients with diagnosed depression (i.e., behavioral activation and cognitive interventions based on an established treatment manual) [26]. The focus on depression was chosen because, on the one hand, it is one of the most prevalent mental disorders [27] and, on the other hand, psychotherapeutic competencies are highly relevant for depression treatment [28, 29].

The study combines the development of SP methods with two consecutive experiments. During the developmental phase, scenarios for the SP portrayals will be developed and validated, instruments for the assessment of therapist behavior and SP authenticity will be developed, SPs will be recruited and trained thoroughly, and their portrayal will be validated on the basis of video recordings.

In the first experiment, two specific training strategies (i.e., reading written instructions with or without modeling) will be compared. In the second experiment, two central supervision techniques (i.e., based on treatment videos versus on verbal reporting) will be evaluated. We expect post-training, psychology students randomly assigned to the active strategy of modeling to display more therapeutic competencies than students who were only reading the written instructions on behavioral activation or cognitive techniques (hypothesis 1). Furthermore, we expect the competence differences between the two groups to persist until the 3-month follow-up (hypothesis 2). Second, we expect that post-supervision, psychology students randomly assigned to supervision based on treatment videos will display more therapeutic competencies than the students who described their treatment verbally to the supervisor (hypothesis 3). Again, we expect the competence differences between the two groups to persist at the 3-month follow-up (hypothesis 4).

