## Methods/Design

### Study design

The study is a single-center RCT (see Fig. 1) in which participants (i.e., bachelor’s and master’s students included as either trainees or supervisees) will conduct therapy sessions with SPs. All sessions will be video-recorded. Following a preparation period, both experiments will be conducted consecutively within a 2-year period. Data will be gathered before and after training/supervision and at the 3-month follow-up. Participants fulfilling the inclusion criteria (see below) will be randomly assigned by computer-generated numbers in a 1:1 ratio and allocated to the experimental or control groups and to the order of the training topics (behavioral activation and cognitive strategies or vice versa). The allocation will be implemented by a researcher (who is independent of the role-plays). The researcher will enroll and assign participants and provide sealed envelopes containing the study material. To reduce the possibility for unblinding, the researcher and student assistants will urge all participants not to speak to any other students about the trial.

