### Statistical analysis and power calculation

To avoid attrition bias, we will include all randomly assigned participants in the primary analyses (intention-to-treat). Second, we will perform per-protocol analyses and compare the results with those from the intention-to-treat analyses. We will use chi-squared tests for nominal data and analyses of variance/analyses of covariance (ANOVAs/ANCOVAs) for ordinal and interval data. For the analysis of training/supervision effects, the ANOVAs will involve a group factor (training/supervision condition) and a time factor (before, after, and follow-up). Possible pre-differences between the groups will be taken into account via the ANCOVAs. The α level will be set at 0.05 and Bonferroni-corrected for multiple testing. Missing data will be addressed according to the outcome and data structure (e.g., complete case analyses and imputation by expectation-maximization or by last observation carried forward).

Considering prior studies [24, 52], we assume moderate competence differences between the groups (Cohens *d* = 0.60) and high correlations between competence ratings (*r* = 0.50). Given an *α* of 0.05 and a 1-*β* of 0.80 (power), a sample of 68 participants will be necessary in each experiment, resulting in an overall sample size of 136 (G*Power Version 3.1.9.2) [53].

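### The stated Bonferroni correction is valid, but Holm's step-down version holds the same familywise error and can only reject more; the size of the gain depends on the test family and the follow-up effect

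*Protocol article*

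**What the plan says.** The section on statistical analysis and power calculation in the protocol article fixes the multiplicity rule in one clause: "The α level will be set at 0.05 and Bonferroni-corrected for multiple testing". It names no step-down, gatekeeping or fixed-sequence procedure and does not say which tests form the family.

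The section on objectives and hypotheses gives each experiment two hypotheses on therapeutic competence. One is a difference after training or supervision (hypotheses 1 and 3). The other is its persistence at three months (hypotheses 2 and 4). For experiment 1 the second reads: "Furthermore, we expect the competence differences between the two groups to persist until the 3-month follow-up (hypothesis 2".

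The planning values are "we assume moderate competence differences between the groups (Cohens *d* = 0.60" and "high correlations between competence ratings (*r* = 0.50", with α = 0.05 and power 0.80. From these the article concludes that "a sample of 68 participants will be necessary in each experiment". Allocation is 1:1, so 34 per arm.

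**The concern.** Single-step Bonferroni holds every test at the reduced level even after another hypothesis in the family has been rejected. Holm's procedure tests the smallest p-value at the Bonferroni level and, once that is rejected, relaxes the level for the next. It controls the familywise error under any dependence between tests, as Bonferroni does, and rejects everything that Bonferroni rejects.

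The difference matters most where two hypotheses must both be shown. A claim of persistence presupposes a difference at post and requires one at follow-up, so the full claim of each experiment rests on that joint result. The sample size was computed at the uncorrected α of 0.05, so there is no spare power to absorb the correction.

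**Working it through.** **Inputs from the article:** d = 0.60, r = 0.50, N = 68 per experiment (34 per arm), α = 0.05, power 0.80, ANCOVA for baseline differences.

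**Assumptions, not in the article:** two-sided tests; a family of two per experiment (post, follow-up), each tested by ANCOVA on baseline; r = 0.50 between every pair of the three ratings; d at follow-up, which is varied below.

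**1. The article's own figure.** For ANCOVA the noncentrality is d/√(1 − r²) × √(N/4) = 0.60/√0.75 × √17 = 2.857 on 65 degrees of freedom. Power at two-sided 0.05 is 80.3%, and 68 is the smallest even N that reaches 80%. A repeated-measures ANOVA between-groups test with two measurements (f = d/2 = 0.30) has λ = 68 × 0.09 × 2/1.5 = 8.16, power 80.4%, and also gives 68. The stated sample size therefore reproduces at uncorrected α.

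**2. Cost of the correction.** The same ANCOVA formula at α = 0.05/2 = 0.025 gives 71.2%.

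**3. What Holm adds with two tests.** Holm rejects one more hypothesis exactly when one p-value is at most 0.025 and the other lies between 0.025 and 0.05. Three results follow:
- the gain for hypothesis i is P(0.025 < pᵢ ≤ 0.05 and pⱼ ≤ 0.025);
- the gain for confirming both is the sum of the two individual gains;
- the chance of rejecting at least one is unchanged.

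Hand check with independent tests and d = 0.60 twice: (0.803 − 0.712) × 0.712 = 0.065 per hypothesis, and 2 × 0.065 = 0.13 for both. Simulated test statistics at zero correlation give 6.4 and 12.8 points.

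**4. Full simulation.** 200,000 replicates, 34 per arm, two ANCOVA p-values per replicate; Monte Carlo error about 0.1 points. Entries are Bonferroni → Holm, in %.

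| d post / follow-up | Post | Follow-up | Both | At least one (either rule) |
|---|---|---|---|---|
| 0.60 / 0.60 | 70.3 → 76.2 | 70.3 → 76.3 | 53.6 → 65.4 | 87.1 |
| 0.60 / 0.45 | 70.5 → 73.7 | 43.8 → 52.1 | 35.3 → 46.8 | 79.0 |
| 0.60 / 0.30 | 70.5 → 71.8 | 19.7 → 26.8 | 16.8 → 25.1 | 73.5 |
| 0.60 / 0 | 70.4 → 70.7 | 2.5 → 4.2 (true null) | n/a | 71.3 |
| 0 / 0 | 2.5 → 2.6 (true null) | 2.5 → 2.6 (true null) | n/a | 4.8 (familywise error) |

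The simulated Bonferroni level (70.3%) is slightly below the formula (71.2%) because the formula ignores chance imbalance in the baseline score.

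**5. Sensitivity.** With r = 0.50 throughout, the two baseline-adjusted test statistics correlate at (0.50 − 0.25)/(1 − 0.25) = 1/3. Varying this from 0 to 0.7, with d = 0.60 at both times, gives gains of 6.4 down to 4.8 points per hypothesis and 12.8 down to 9.7 for both. Without baseline adjustment the gains are 5.5 to 6.2 and 11.1 to 12.4 points. With all four hypotheses in one family they are about 10 to 11 points per hypothesis and 16 to 18 for post and follow-up of one experiment together.

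**The case against.** **Bonferroni is standard and controls the error rate, and a condensed article may leave the algorithm and the family to a fuller plan.** The first half stands: nothing here is invalid. On the second, the undefined family is not the complaint. The article does name a rule, and its plain reading is the single-step one. If a fuller plan already specifies the step-down form, the point is met.

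**The figures rest on an assumed family and on equal effects.** This stands. The article describes ANOVAs with group and time factors, lists many secondary outcomes, and gives one d without saying that it applies at both times. A reader might infer that the trial certainly loses about 6 points per hypothesis and 11 to 12 for the pair. The documents do not support that as a fact: the post gain falls to about 3, 1 and 0.2 points when the follow-up effect is 0.45, 0.30 or 0. Only the direction is general.

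**Bonferroni is not inferior in every respect.** This also stands. Its simultaneous intervals are simple and match its tests. Ordinary 95% intervals beside Holm-adjusted p-values can disagree with the decision: when both p-values lie between 0.025 and 0.05, both intervals exclude zero and Holm rejects neither. With d = 0.60 at both times that happens in about 1% of replicates.

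**Fixed-sequence testing (post, then follow-up, each at 0.05) fits the persistence logic at least as well.** In the same setting it gives 79.6% for post and about 66% for both, slightly better than Holm. It is a reasonable choice, but a real trade-off: if post fails, follow-up cannot be claimed, so at least one hypothesis is confirmed in 79.6% of replicates rather than 87.1%. This does not alter Holm's advantage over the stated rule, since Holm keeps every rejection that Bonferroni makes.

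**Conclusion.** The point holds as an efficiency improvement. For decisions to reject or not, Holm is at least as powerful as the stated rule whatever the effects, correlations or family, with the same familywise error (4.8% for either rule under the global null in the setting above).

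Its size is conditional. With a family of two per experiment, d = 0.60 at both times, N = 68, r = 0.50 and ANCOVA, power rises from about 70% to 76% per hypothesis and from about 54% to 65% for both. With follow-up d = 0.45 the gains are about 3 points (post), 8 points (follow-up) and 11 points (both). If only the post effect exists the gain is negligible. The chance of at least one confirmed hypothesis is the same throughout.

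Two stronger readings should be resisted. The stated correction does not inflate error. Nor does Holm recover the planned 80%: power per hypothesis stays near 76% even in the favourable case, because 68 was derived at uncorrected α. That is a separate matter.

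**What to change.** In the statistical analysis section, replace the Bonferroni wording by Holm correction (step-down Bonferroni) and state that it applies within each experiment to the post and follow-up tests of competence. The smaller p-value is tested at 0.025 and, if rejected, the other at 0.05. Make the change before outcome data are analysed and report it as a protocol modification, for which the trial status section already provides a route.

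The cost is a short wording change, with no additional participants or data. The small downside is the loss of simple simultaneous intervals that match the tests. Report ordinary 95% intervals beside the Holm-adjusted p-values, label them as unadjusted, and note that they can occasionally disagree with the Holm decision.

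### Last observation carried forward and complete-case analysis are not excluded from the primary competence analysis; the former would favour the two persistence hypotheses if the effect fades

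*Protocol article*

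**What the plan says.** All of the analysis text is in the section Statistical analysis and power calculation. On the analysis set it says: "To avoid attrition bias, we will include all randomly assigned participants in the primary analyses (intention-to-treat"). Per-protocol analyses follow for comparison. Training and supervision effects are tested by ANOVA with a group factor and a time factor of three levels, and ANCOVA is used for baseline differences.

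On missing data it says: "Missing data will be addressed according to the outcome and data structure". The examples in brackets are "complete case analyses and imputation by expectation-maximization or by last observation carried forward". No method is tied to a particular outcome or time point, and none is confined to secondary or sensitivity analyses.

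Under Objectives and hypotheses, hypothesis 2 (training) reads: "we expect the competence differences between the two groups to persist until the 3-month follow-up". Hypothesis 4 says the same for supervision. Under Duration, the pre- and post-measurements fall in one appointment of 3.5 h and the follow-up is a separate visit. Under Participants, withdrawal is possible at any time. No dropout rate is given.

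**The concern.** Because the first two role-plays share a visit, most missing competence scores are likely to be 3-month scores, and the last available value will normally be the post score. Carrying it forward assumes that the participant's competence did not change over the 3 months. Hypotheses 2 and 4 ask whether the group difference lasts over that period, so for every participant lost to follow-up LOCF supplies the answer by assumption.

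Complete-case analysis raises a different problem. It leaves out randomised participants whose follow-up is missing, whereas the primary analysis is meant to include everyone so as to avoid attrition bias.

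Two of the four hypotheses depend on the 3-month comparison. A missing-data method that can produce or enlarge that difference should not remain available for it.

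**Working it through.** **Inputs from the protocol article.** d = 0.60, r = 0.50, α = 0.05, power 0.80 and 68 participants per experiment (statistical section); 1:1 allocation (Study design), so 34 per arm. **Assumed:** 5 to 30% missing at 3 months, completely at random; standardised scores with SD 1; the same correlation of 0.50 between every pair of time points.

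**The plan's own figure.** For the between-group effect in a repeated-measures ANOVA with f = d/2 = 0.30 and m = 2 measurements, λ = N·f²·m / (1 + (m − 1)·r) = 68 × 0.09 × 2 / 1.5 = 8.16. With 1 and 66 degrees of freedom the power is 0.804, and 68 is the smallest even N that reaches 0.80. The sample size reproduces and is not in question here.

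**Bias formula.** Let q be the share missing, D_post the post difference and D_fu the true 3-month difference. The expected difference after LOCF is (1 − q)·D_fu + q·D_post, so the bias is q·(D_post − D_fu).

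- Complete fading (D_fu = 0): 0.10 × 0.60 = 0.06; 0.20 × 0.60 = 0.12; 0.30 × 0.60 = 0.18 SD.
- Half fading (D_fu = 0.30): 0.03, 0.06 and 0.09 SD, giving 0.33, 0.36 and 0.39.
- Constant (D_fu = 0.60): bias 0.
- Growing (D_fu = 0.80): −0.02, −0.04 and −0.06 SD, giving 0.78, 0.76 and 0.74, which works against the hypotheses.

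If persistence is tested instead as the group difference in change from post to follow-up, LOCF sets that change to zero for each missing participant. The contrast is multiplied by (1 − q): at 20% missing, a true fading of 0.60 appears as 0.48.

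**Error rates.** These come from 20,000 simulated trials per setting, 34 per arm, with a two-sided ANCOVA of the 3-month score on baseline. For complete fading:

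| Missing | LOCF estimate (SD) | Rejection at 0.05, LOCF | Rejection at 0.05, observed only | Rejection at 0.025, LOCF |
|---|---|---|---|---|
| 5% | 0.03 | 5.3% | 5.0% | about 2.6% |
| 10% | 0.06 | 5.8% | 4.9% | 3.2% |
| 20% | 0.12 | 8.3% | 5.0% | 4.6% |
| 30% | 0.18 | 12.8% | 5.1% | 7.9% |

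The 0.025 column is included because the plan applies a Bonferroni correction without giving the number of tests; 0.025 is an assumption.

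For half fading at 0.05, LOCF rejects in 33, 39 and 44% of trials at 10, 20 and 30% missing, against 26, 24 and 21% on observed scores. A true difference exists here, so these are not false positives, but the estimated difference is too large.

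**Complete cases.** At 20% missing, 0.80 × 68 = 54.4, so about 54 of 68 participants remain. Under missingness completely at random this gave an unbiased estimate and cost only power. The conflict is with the stated analysis set, and bias becomes possible if dropout is related to competence.

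**The case against.** The strongest reply is that the plan commits to none of this. The methods are examples, the sentence covers every outcome from alliance to knowledge tests, and LOCF is never tied to the competence score or to follow-up. The document is a condensed article, and a statistical analysis plan may assign the methods. This stands as a limit: the finding concerns a method the plan permits and does not exclude. It is still more than missing detail, because a method named as acceptable gives a biased 3-month result when the effect fades.

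A reader might infer several stronger points that the text does not support:

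- **That the plan contradicts its own intention-to-treat statement.** Complete-case analysis could be meant for the per-protocol analyses or secondary outcomes. The conflict arises only if it is used for the primary analysis.
- **That the method will be chosen after the data are seen.** The wording also fits a rule set in advance by type of outcome, and no timing is given.
- **That expectation-maximization means a single fill-in treated as observed.** The text does not say so.
- **That LOCF bias and loss of cases occur together.** Within one analysis they exclude each other: imputed cases are not dropped. An ANCOVA of post on baseline does not need the follow-up score, so a loss of power for hypotheses 1 and 3 does not necessarily follow.
- **That LOCF always favours persistence.** It does so only if the difference shrinks after post.

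The size also depends on dropout. The plan offers course credit or €40 and intends to promote retention, and at 5 to 10% missing the inflation is small.

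**Conclusion.** The point holds in a limited form and should be fixed. LOCF is left open for the 3-month competence analysis, where it would pull the group difference toward the post difference and favour hypotheses 2 and 4 whenever the effect fades. The figures of 0.06 to 0.18 SD and about 6 to 13% type I error are a worst case: complete fading from 0.60, an assumed 10 to 30% missing, and no multiplicity correction. They should not be read as the trial's expected error rates. Against an assumed corrected level of 2.5%, the corresponding rates are about 3 to 8%. Fading cannot be ruled out in advance, since whether it occurs is the question being tested. The complete-case point is conditional on its use as the primary analysis.

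**What to change.** State, before the follow-up data are analysed, that:

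1. LOCF is not used for the 3-month competence analysis.
2. The primary method is a likelihood-based linear mixed model with group, categorical time and baseline, fitted to all observed scores of all randomised participants. A participant with a post score then stays in the analysis when the follow-up is missing. The model is valid if missingness depends only on observed scores (missing at random).
3. Complete-case analysis is confined to a labelled sensitivity analysis.
4. Multiple imputation may be added as a further, optional sensitivity analysis.

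The cost is a change of wording and slightly more analysis work. No new data are needed and the sample size is not affected. The Trial status section already provides for reporting protocol modifications.

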## Discussion

This RCT combines the investigation of specific training and supervision techniques in clinical psychology by using SPs and a validated observer-based rating scale for the assessment of psychotherapeutic competencies. We thus expect the study to contribute to evidence-based education and training in the treatment of mental disorders [1]. Developing SP scenarios for the field of clinical psychology, gathering knowledge in the use of SPs, and assessing competencies within standardized encounters will contribute to further developments within our field.

SPs enable approximating clinical encounters but may not replace them. Therefore, external validity will be lower in this study than in patient studies. The legal regulations for qualification and licensure of psychotherapists are about to be reformed by the German Federal Ministry of Health. In the draft law, practical education is extended even within the master’s program [54], which will require evidence-based knowledge on effective training strategies. Above and beyond that, professional bodies such as the American Psychological Association [55] require obtaining and enhancing therapeutic competencies during profession-long learning. Therefore, the results might contribute to the development of licensed therapists and thus to the effective treatment of mental health patients.

## Trial status

This is the first protocol version (10 December 2019). Recruitment of participants started on 4 December 2019 and will end when a complete sample size is attained (around 31 December 2021). If protocol modifications prove necessary, we will communicate them within the study publications and the final report to the funder.

## Abbreviations

ANCOVA: Analysis of covariance
ANOVA: Analysis of variance
CBT-AS: Cognitive Behavioral Therapy Adherence Scale
MCQ: Multiple-choice question
PI: Principal investigator
RCT: Randomized controlled trial
SP: Simulated/standardized patient
